## 10.2 SAFETY MONITORING AND REPORTING

The principles of ICH GCP require that both investigators and sponsors follow specific procedures when notifying and reporting adverse events or reactions in clinical trials.

### 10.2.1 Definitions

The following definitions apply to this protocol:

#### 10.2.1.1 Adverse Event (AE)

Any untoward medical occurrence in a patient or clinical trial subject administered a medicinal product and which does not necessarily have a causal relationship with this treatment.

#### 10.2.1.2 Adverse Reaction (AR)

Any untoward and unintended response to an investigational medicinal product related to any dose administered.

Comment: All adverse events judged by either the reporting investigator or the sponsor as having a reasonable causal relationship to a medicinal product would qualify as adverse reactions. The expression 'reasonable causal relationship' means to convey, in general, that there is evidence or argument to suggest a causal relationship.

#### 10.2.1.3 Serious Adverse Event (SAE) or Serious Adverse Reaction (SAR)

Any adverse event or adverse reaction that results in death, is life-threatening\*, requires hospitalisation or prolongation of existing hospitalisation, results in persistent or significant disability or incapacity, or is a congenital anomaly or birth defect.

Comment: Medical judgement should be exercised in deciding whether an adverse event/reaction should be classified as serious in other situations. Important adverse events/reactions that are not immediately life-threatening or do not result in death or hospitalisation, but may jeopardise the subject or may require intervention to prevent one of the other outcomes listed in the definition above, should also be considered serious.

\*Life-threatening in the definition of a serious adverse event or serious adverse reaction refers to an event in which the subject was at risk of death at the time of the event. It does not refer to an event which hypothetically might have caused death if it were more severe.

#### 10.2.1.4 Suspected Unexpected Serious Adverse Reaction (SUSAR)

An adverse reaction that is both unexpected (not consistent with the applicable product information) and also meets the definition of a Serious Adverse Event/Reaction.

#### 10.2.1.5 Intensity

The intensity of each AE recorded in the case report form should be assigned to a grade (1-5), which will be determined following the definitions set forth in the Common Terminology Criteria for Adverse Events v3.0 (CTCAE) (Cancer Therapy Evaluation Program, 2006). Use of these standardized guidelines will allow for uniform reporting. The grades are defined as follows:

- Grade 1: Mild AE
- Grade 2: Moderate AE
- Grade 3: Severe AE
- Grade 4: Life-threatening or disabling AE
- Grade 5: Death related to AE

#### 10.2.2 Identifying, managing adverse events

Participants who develop adverse events as a consequence of the study interventions or other treatments will be identified at follow-up visits and referred to the designated hospital for evaluation and treatment according to local guidelines. Mild adverse events will be noted in the participant's case report form; no further action will be taken by study staff except in the case of vomiting, in which case the study medication may need to be re-administered. In the case of any SAE, subjects will be referred to the hospital for management. Transportation to the hospital will be provided where feasible or transport reimbursed. All participants with SAEs will undergo record review to identify potential adverse consequences of study participation.

#### 10.2.3 Assessment of causality

The investigator is obligated to assess the relationship between investigational product and the occurrence of each AE/SAE. The investigator will use clinical judgment to determine the relationship. Alternative causes, such as natural history of the underlying diseases, concomitant therapy, other risk factors, and the temporal relationship of the event to the investigational product will be considered and investigated. The investigator will also consult the drug information and the DMEC as needed in the determination of his/her assessment.

There may be situations when an SAE has occurred and the investigator has minimal information to include in the initial report. However, it is very important that the investigator always make an assessment of causality for every event prior to transmission of the SAE report. The investigator may change his/her opinion of causality in light of follow-up information, amending the SAE case report form accordingly.

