### 10.1 DATA MONITORING AND TRIAL OVERSIGHT COMMITTEES

#### 10.1.1 Data Monitoring and Ethics Committee (DMEC)

Since the study is a clinical trial an independent Data Monitoring and Ethics Committee (DMEC) will be set up. The DMEC will be critical to ensure that the subjects are protected from harm, while also

ensuring that the study integrity is not compromised. The DMEC will consist of 3 to 4 independent members knowledgeable in the conduct of clinical trials. They will meet regularly (e.g. twice yearly or more frequent if so required) during data collection period to provide a review of blinded (and if requested unblinded) data to ensure the safety, rights and well-being of trial participants. In addition, regular review of the quality of the study data will be conducted at each meeting of the DMEC.

The roles and membership of the DMEC are described in more detail in Appendix II. Terms of reference oversight committees, section 16.2, page 71.

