##### 10.1.3.2 Interim analysis

An interim analysis will be conducted on the primary endpoint when approximately 75% of participants have enrolled or at a time point suggested by the TSC or DSMB. The interim-analysis will be performed by an independent statistician, blinded for the treatment allocation. The statistician will report to the independent DMEC. The DMEC will have unblinded access to all data and will discuss or report the results of the interim-analysis with the Trial Steering Committee (TSC), e.g. in a joint meeting. The TSC decides on the continuation of the trial and will report to the ethics committees.

The Lan-DeMets spending function with O'Brien-Fleming type boundaries will be employed and the sample size inflated (see 7.6.1.2, page 37) to preserve the overall one-sided type I error rate for efficacy at the  $\alpha=0.05$  level at the final analysis. If the stopping boundary is crossed at the interim analysis and the RR is less than 1, i.e. the observed prevalence of the primary endpoint in the intervention arm is less than the expected prevalence under the null hypothesis, it will be concluded that the study has demonstrated that the efficacy of the intervention is superior to that of IPTp-SP in the prevention of the primary outcome. The trial recruitment can then be stopped unless the DMEC advises otherwise. Statistics will not be the sole basis for the decision to stop or continue and the DMEC can advise to continue recruiting in the trial (e.g. in 2 of the 3 arms), or stop recruiting but continue to complete the intervention as per randomization in the remaining active women, even if statistically the stopping boundary is crossed, e.g. in order to continue collecting more safety

information or data for further sub-group analyses etc. The trial will not be stopped in case of futility, unless the DMEC during the course of safety monitoring advises otherwise.

A detailed plan for interim analysis, the provisional stopping rules and how the stopping rules will be applied, will be drawn up prior to the start of the interim analysis and documented in the study statistical analysis plan.

In addition, regular review of the quality of the study data will be conducted at each meeting of the DMEC.

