#### 10.2.4 Reporting adverse event procedures

All SAEs will be reported to the in country principal investigator or an assigned representative within 24 hours of the staff becoming aware of it, using an SAE form, which should be completed and sent electronically. The SAE form asks for nature of event, date of onset, severity, corrective therapies given, outcome and causality (i.e. unrelated, unlikely, possible, probably, definitely). The responsible study clinician should assign the causality of the event.

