##### 10.2.4.1 Expedited reporting

SAEs that are unexpected and are at least 'possibly related' to the study drug require expedited reporting within 24 hours of the country principal investigator or assigned representative becoming aware of it (e-mail notification); i.e. this will be a maximum of 48 hours after the event occurred or the study team were made aware of the event (including the 24 hours required for the field staff to report to the principal investigator / representative). Additional information will be sent within 14 additional days (full SAE report) if the reaction had not resolved at the time of e-mail notification.

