## 10.4 OTHER QUALITY CONTROL MEASURES

### 10.4.1 Safety monitors

A local paediatrician and/or obstetrician will act as trial safety monitors, one per country.

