### 16.2.3.2 Role DMEC

The DMEC consist of 3-4 members (including one or more clinicians and one statistician, all with experience in clinical trials).

The DMEC shall assess the data regularly (before the annual TSC meeting) to review the data and the interim analysis. The assessment could be via email or other electronic medium annually prior to the TSC meeting. In the first year of recruitment more frequent assessment (bi-annually) is recommended for this trial with one face to face meeting at least once during the trial.

The members should be the only personnel to see the results separated by treatment group during the trial. They are independent and look at the trial from an ethical point of view of the participant safety, future participants and society in general. It is their responsibility to prevent participants being exposed to any excess risks by recommending to the Trial Steering Committee (TSC) for the trial suspension or termination early if the safety or efficacy results are sufficiently convincing. The trial statistician is usually invited to attend part of the DMEC meeting to present the most current data from the trial. This will be blinded, unless the DMEC specifically requests for an unblinded analysis.

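### Section 10.2.3 has investigators consult the DMEC on the causality of individual events, opening an unneeded route between a committee that may hold data by arm and the blinded sites

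*Protocol*

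**What the plan says.** Section 10.2.3 makes the investigator responsible for judging the relation of each AE or SAE to the investigational product, and adds: "The investigator will also consult the drug information and the DMEC as needed in the determination of his/her assessment". Section 10.2.4 keeps the grade with the site: "The responsible study clinician should assign the causality of the event".

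The DMEC's position is described in several places:

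- Section 10.1.1 provides for regular "review of blinded (and if requested unblinded) data to ensure the safety, rights and well-being of trial participants".
- Section 10.1.3.2, on the interim analysis, states: "The DMEC will have unblinded access to all data".
- Section 16.2.3.2 states: "The members should be the only personnel to see the results separated by treatment group during the trial". Of the members it adds: "They are independent and look at the trial from an ethical point of view of the participant safety, future participants and society in general". It also says that the data shown to the committee are blinded unless the committee specifically asks otherwise.
- Section 8.2.2 allows the DMEC to carry out individual unblinding so that the sponsor and trial team stay blinded.
- Section 10.2.4.3 has safety data reported to the DMEC. Section 16.2.3.3 has the DMEC report to the TSC and recommend whether the trial continues, is modified or stops.

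The grade has consequences. Under 10.2.4.1, "SAEs that are unexpected and are at least 'possibly related' to the study drug require expedited reporting". Under 10.2.4.2, common illnesses that do not lead to hospital admission are left out of the aggregated report unless they are at least possibly related.

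Section 10.4.1 already provides another possible adviser: "A local paediatrician and/or obstetrician will act as trial safety monitors, one per country".

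**The concern.** A data monitoring committee's safety review is useful because its members see comparative data that the sites do not, and because they had no hand in producing the data they judge. Section 10.2.3 weakens both conditions for one item, the causality grade. It creates direct contact, about an identified woman, between a blinded investigator and members who may know how events are falling by arm.

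Three things are at stake:

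- **The grade.** Advice from someone who has seen an imbalance between arms may reflect that imbalance rather than the clinical facts of the case. The reporting triggers then act on a grade shaped that way.
- **The AZ masking.** Section 8.2.1 gives AZ as the only placebo-controlled element, so this is the blinding a reply could damage. SP versus DP allocation is not concealed by placebo in any case.
- **The committee's independence.** It would later review safety data containing relatedness judgements on which it had advised.

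**Working it through.** No arithmetic bears on this point. The check is to set the sections side by side.

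1. **Is consultation a stated rule?** Yes. Section 10.2.3 directs it, when needed, and the sentence belongs to the assessment of each event. It is case-level advice, not aggregate review.

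2. **Can the DMEC hold data by arm when asked?** Yes, but not always. Sections 10.1.1 and 16.2.3.2 make routine review blinded, with unblinding on request. Section 10.1.3.2 gives full unblinded access at the interim analysis, planned at about 75% enrolment. From whichever comes first, members may know results by arm.

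3. **Can the DMEC hold an individual code?** Yes. Section 8.2.2 requires unblinding before a SUSAR is notified and lets the DMEC perform it. By 10.2.1.2 and 10.2.1.4, SUSAR status itself depends on a causality judgement. Section 10.2.3 lets the investigator revise that judgement on follow-up information. For one event, then, the DMEC could hold the code and later be asked about relatedness by the blinded investigator.

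4. **Does any section restrict the consultation?** None confines it to blinded information, to a member without access by arm, or to an intermediary.

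5. **Does consultation fit the DMEC's working pattern?** Poorly. A grade must precede transmission of the SAE report (10.2.3), and SAEs are reported within 24 hours of staff becoming aware (10.2.4). The DMEC meets about twice yearly (10.1.1). Advice before the first report would need ad hoc contact with members. Advice on a later amendment of the grade is more plausible.

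6. **Is it among the DMEC's listed duties?** No. Section 16.2.3.3 lists interim data, unblinding requests and reports to the TSC. The list is not exhaustive, because 7.3.2.2, 7.3.5.1 and 8.2.2 give the DMEC other participant-level roles.

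7. **Where does the grade go?** Into expedited reporting (10.2.4.1), into the aggregated report (10.2.4.2), and back to the DMEC with the safety data (10.2.4.3).

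8. **Does the grade enter a planned efficacy or safety comparison?** Not in the protocol. The primary outcome (7.4.1, 9.1.1) is built from foetal loss, birthweight, ultrasound-dated gestation and neonatal death. The safety outcomes (7.4.2.2) include SAEs and AEs without regard to relatedness, and 9.3.2.2 gives the number of SAEs as its example of a count outcome.

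Steps 1 to 4 establish the open route. Steps 2, 5 and 8 limit how much it matters.

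**The case against.** The strongest reply is that this is one permissive clause with little practical reach. Consultation happens only when needed, the clinician owns the grade, routine DMEC review is blinded unless the committee asks otherwise, and the 24-hour deadline makes DMEC input to a first grade unlikely. The DMEC also has other participant-level roles, so a case-level function may have been intended. An ordinal opinion on relatedness reveals an AZ allocation only if a member knows that woman's code and lets it show. All of this stands, and it sets the size of the point. It does not close the route, because nothing in the protocol restricts what the consulted members may know.

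A reader might infer more than the text supports:

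- **That the DMEC sets the relatedness data.** It can influence a grade. Section 10.2.4 leaves assignment with the study clinician.
- **That the DMEC is the only body that can see results by arm.** Section 16.2.3.2 says it should be, but 10.1.3.2 has it discuss or report interim results with the TSC.
- **That the DP+AZ versus DP comparison of the primary outcome is undermined.** Causality plays no part in that outcome, which 8.2.1 describes as objective.
- **That the number of such contacts can be estimated.** The protocol gives no referral rate, so any count would be invented.

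There is also a fair objection to simply substituting the country safety monitor. Section 8.2.2 excepts correspondence with the safety monitor or the DMEC chair from its bar on disclosing a code. The monitor cannot be assumed blinded for every woman, and the fix must allow for that.

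**Conclusion.** The point stands as a modest weakness in a stated rule. Section 10.2.3 brings into case-level causality grading a committee that may hold data by arm, may hold individual codes, and must review the graded data independently. What is exposed is the expedited-reporting trigger, the filter on the aggregated report, the AZ masking at sites and the committee's distance from the data it reviews. It is a possible route, not a planned disclosure, and no analysis described in the protocol uses the causality grade.

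The conclusion rests on two readings: that consultation means contact about an individual event, as the sentence's place in 10.2.3 implies, and that members consulted may have seen data by arm, which 10.1.1, 10.1.3.2 and 16.2.3.2 allow. An SOP or DMEC charter confining such advice to blinded information would remove most of the concern, but the protocol text does not do so. The case for acting is that the route serves no purpose that a blinded adviser could not serve.

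**What to change.** 1. In 10.2.3, delete the reference to the DMEC. Direct causality queries to a medical adviser with no access to results by arm or to that woman's allocation. The country safety monitor in 10.4.1 can serve, except where the monitor has received that woman's code under 8.2.2; another blinded medical reviewer should then advise.
2. State that the DMEC receives causality grades with the safety data but does not advise sites on grading individual events.
3. Reconcile this with the other sections that give the DMEC a participant-level role: 7.3.2.2 and 7.3.5.1 on withdrawal from therapy, and 8.2.2 on unblinding. The limit in item 2 concerns causality grading only and takes no position on those rules.

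The cost is a few sentences in the next amendment and a named back-up reviewer. The safety monitors are already provided for, and the DMEC's oversight of safety is unchanged.

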#### 10.2.4 Reporting adverse event procedures

All SAEs will be reported to the in country principal investigator or an assigned representative within 24 hours of the staff becoming aware of it, using an SAE form, which should be completed and sent electronically. The SAE form asks for nature of event, date of onset, severity, corrective therapies given, outcome and causality (i.e. unrelated, unlikely, possible, probably, definitely). The responsible study clinician should assign the causality of the event.

##### 10.2.4.1 Expedited reporting

SAEs that are unexpected and are at least 'possibly related' to the study drug require expedited reporting within 24 hours of the country principal investigator or assigned representative becoming aware of it (e-mail notification); i.e. this will be a maximum of 48 hours after the event occurred or the study team were made aware of the event (including the 24 hours required for the field staff to report to the principal investigator / representative). Additional information will be sent within 14 additional days (full SAE report) if the reaction had not resolved at the time of e-mail notification.

#### ***10.2.4.2 Scheduled reporting***

Other SAEs and AEs will be reported annually (or more frequent if so required by the DMEC or ethics committees) in an aggregated report. AEs that will not be reported include common illnesses that do not result in hospitalization, including but not limited to clinical malaria, respiratory, gastrointestinal, and skin diseases, unless they are considered at least possibly related to the intervention.

#### ***10.2.4.3 Recipients of reports***

The study will comply with local regulations pertaining to reporting of SAEs to their local Research Ethics Committee and/or Research & regulatory offices. In addition to the primary ethics committees, we will report safety data to the DMEC, and to the sponsor. In addition, and if so requested by the manufacturer, the sponsor will forward the reports to the manufacturers of DP (Sigma Tau) and to the manufacturer of AZ. A copy of the final study report will be provided to all study hospitals, ethics committees, TSC, DMEC, to local regulators, and, if so requested, to Sigma Tau and the manufacturer of AZ.

Figure 1: Safety reporting assessment flowchart[figure not shown]

IMP: Investigational Medicinal Product

\*See definition of SAE in section 10.2.1

\*\*Assessed in line with the current approved Investigator's Brochure (IB)

## 10.3 TRIAL MONITORING AND AUDITING

### 10.3.1 Trial monitoring

External clinical trial monitoring visits are provided by the sponsor at trial initiation, and then regularly (at least yearly) thereafter and at trial close out, or more frequently if so required; e.g. if the trial field work is about 24 months, this means that each site is visited approximately 4 times by external monitors. The results from each monitoring visit will help inform whether more frequent or earlier repeat visits are required. The frequency of these visits appeared appropriate for our experienced study sites in recent trials and the feedback was highly appreciated by the study teams.

### 10.3.2 Auditing

The independent clinical monitoring process will be audited by a study staff from the sponsor's research office at LSTM in Liverpool, UK. The auditor will accompany the clinical monitor during at least one of the site visits. After this visit it will be determined by the sponsor if more auditing visits are required.

### 10.3.3 Role of sponsor

The sponsor reserves the right to suspend temporarily or prematurely discontinue this study at any time for reasons including, but not limited to, safety or ethical issues or severe non-compliance. If the sponsor determines such action is needed, it will discuss this with the investigator. When feasible, the sponsor will provide advance notification to the investigator of the impending action prior to it taking effect. The sponsor will promptly inform the ethics committees and provide the reason for the suspension or termination.

## 10.4 OTHER QUALITY CONTROL MEASURES

### 10.4.1 Safety monitors

A local paediatrician and/or obstetrician will act as trial safety monitors, one per country.

### 10.4.2 Internal monitoring

Each of the partner's institutions have their own internal quality control teams who will conduct internal monitoring on a regular basis, and also to help prepare for external monitoring visits.

